### Variable library

Exposures, outcomes and covariates of interest will be identified using medical coding (Read/SNOMED/EMIS), product coding (DM+D) and recording of patient death or transfer out of a participating practice in CPRD Aurum. The final definitions and code library has been drawn up and validated through consensus agreement among all investigators.

### Sample size calculation

The estimated median follow-up time for the *exposed* with a weight Read code in their record in the 1 year *before* the index date is 3.2 years (mean: 4.6), which is based on our feasibility work for this project. We assumed a 1% annual incidence rate of CVD meaning 3% of the study population would develop CVD over the 3.2 years of follow-up.^30^ We also assumed a relative risk (RR) of 1.3 for CVD in the *exposed* versus *unexposed*.^31^ The n ratio was set at 0.25, which achieved the best balance between statistical power and data cost. Our calculation suggested a minimum sample size of n=3907 at 80% power to detect an RR of 1.3, alpha <0.05%. Our feasibility estimates indicate that there are 135 870 patients with SMI in CPRD Aurum, meaning the study is sufficiently powered to detect small effects.

### Statistical analysis

Analyses will be conducted in Stata using an estimation approach. We do not intend to impute missing data. The entry date into the analysis is the index date. The outcome date is the earliest of: (1) the date of death or (2) date of diagnosis of the outcome of interest. For objectives 1 and 2, we will use all repeated measures and run separate models for each analyses. For objective 3, we will use the first recorded diagnosis of the outcome of interest rather than recurrent events. Patients who do not have the outcome of interest will be censored at the earliest of: (1) date of death, (2) date of leaving the practice, (3) date of the latest download of data or (4) the study end date.

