### Outcomes

The primary aim of objective 1 is to assess the impact of an SMI diagnosis on weight change. A pilot search of the database indicated waist circumference was not reliably recorded so we did not include this as a measure of adiposity. The outcome for objective 2 is change in cardio-metabolic risk factors for CVD, which include change in systolic and diastolic blood pressure, change in total cholesterol/high-density lipoprotein ratio, and change in glycaemia indicated by HbA1c or fasting glucose. The outcome for objective 3 is incidence of and mortality from CVD. The objective for 4 is coded weight management advice and referral to weight management services. We will interpret the data based on the associations for all outcomes, as well as consistency and interpretable patterns. The specific outcomes for each objective are outlined in table 1.

**Table 1 T1:** Outcome measures

Objective	Outcome	Measures
Objective 1: Examine the association between SMI and weight change	Weight change	Absolute mean weight change (kg)
		Percentage weight change (kg)
		Change in body mass index (kg/m^2^)
Objective 2: Examine the association between SMI and changes cardio-metabolic risk factors for CVD	Cardio-metabolic risk	Change in fasting blood glucose (FBG)
		Change in haemoglobin A1c (HbA1c)
		Change in mean total-cholesterol
		Change in triglycerides
		Change in low-density lipoprotein (LDL)
		Change in blood pressure (systolic (SBP) and diastolic (DBP))
Objective 3: Total incident and fatal CVD	Incidence of CVD and CVD fatalities	Angina diagnosed by GP
		Acute coronary syndrome
		Coronary heart disease
		Congestive heart failure
		Cardiomyopathy
		Total stroke
		Total fatal CVD events
Objective 4: Weight management advice and service referral	Proportion (%) of exposed and unexposed who are recorded as offered advice, and then offered and actually referred to a weight management service	

CVD, cardiovascular disease; GP, general practitioner; SMI, serious mental illness.

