#### Primary analyses

For objectives 1 and 2, the outcome will be visually inspected by plotting trajectories of weight and cardio-metabolic risk factor change using all repeated measurements for patients with SMI versus patients without SMI. For these analyses, we will use a mixed-effects linear regression model including terms for SMI, time and their interaction to estimate regression coefficients with 95% CIs by SMI status. Models incorporating psychotropic medications will analogously include medication-time multiplicative interaction terms. We will include a random effect for individual and practice identifier to account for intra-class correlation resulting from common practice membership. Diagnostic tests will be conducted to confirm linear regression assumptions are met including linearity of residuals, residual normality using quantile–quantile (Q–Q) plots, and residual heteroscedasticity using residual versus fitted value plots. We will assess for exploratory subgroup effects by adding interactions (eg, by age, sex, ethnicity and SES) and, if significant, we will assess the strength of the associations in separate subgroups for clarity. For objective 2, we will model the association between weight and cardio-metabolic change using restricted cubic splines to allow for non-linear associations. For objective 3, we will use Kaplan-Meier survival estimates for the exposed and unexposed groups to estimate the distribution of time from index date to total and fatal CVD and mortality (all-cause). The statistical equivalence of the two curves will be examined using the log-rank test. This analysis will use a survival from index date between the exposed and unexposed groups using an adjusted Cox proportional hazards regression model with follow-up time as the timescale. Restricted cubic splines will be computed with five knots to visually explore non-linear associations between the exposure and the outcomes. For objective 4, we will use a Poisson regression examining person-time to estimate the rate at which patients who received weight management services over the study period in patients with SMI compared with patients who do not have SMI, adjusting for confounders and BMI.

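### The Statistical analysis section contradicts itself on whether death is an event or a censoring time for objective 3, so the event must be defined endpoint by endpoint

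*Protocol article*

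**What the plan says.** Two rules on death stand in the opening paragraph of Statistical analysis.

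- Outcome date: "The outcome date is the earliest of: (1) the date of death or (2) date of diagnosis of the outcome of interest".
- Censoring: "Patients who do not have the outcome of interest will be censored at the earliest of: (1) date of death", followed by leaving the practice, the last data download and the study end.

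The same paragraph says: "For objective 3, we will use the first recorded diagnosis of the outcome of interest rather than recurrent events".

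Elsewhere in the article:

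- Outcomes: "The outcome for objective 3 is incidence of and mortality from CVD". The only fatal item in Table 1 is "Total fatal CVD events".
- Duration of follow-up lists death and the outcome of interest as two separate ends of follow-up.
- Primary analyses, for objective 3: "we will use Kaplan-Meier survival estimates for the exposed and unexposed groups". The endpoints named there are total CVD, fatal CVD and, as a separate item, all-cause mortality. A log-rank test follows, then a regression "using an adjusted Cox proportional hazards regression model with follow-up time as the timescale". No competing-risk method is named.
- Descriptive summaries groups causes of death as CVD and all-cause, with no non-CVD group.
- Data linkage includes the Office for National Statistics (ONS) mortality data.

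**The concern.** If any death sets the outcome date, no patient can be left to be censored at death. If patients without the outcome are censored at death, death alone cannot have been the outcome. An analyst who follows the paragraph must choose one rule and break the other.

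The choice matters because objective 3 asks about CVD. Under the outcome-date rule read literally, a patient who dies of cancer or an accident contributes an event to a CVD analysis. The hazard ratio then describes CVD or death, and fatal CVD becomes indistinguishable from all-cause mortality. Under the censoring rule the Cox model answers the intended question, but the Kaplan-Meier curves for CVD do not give the absolute risk that readers will take from them. Patients who died of other causes are treated as if they could still develop CVD.

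**Working it through.** **1. The plan's own figure.** Sample size calculation gives 3% CVD over follow-up, relative risk 1.3, ratio 0.25 and 80% power. With p0 = 0.03, p1 = 0.03 × 1.3 = 0.039, r = 0.25 and pooled p = (0.03 + 0.25 × 0.039)/1.25 = 0.0318:

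n0 = [1.960 × √((1 + 1/r) × p(1 − p)) + 0.842 × √(p0(1 − p0) + p1(1 − p1)/r)]² / (p1 − p0)² = 15,628 unexposed.

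Exposed = 0.25 × 15,628 = 3,907, the printed number. The match is to the exposed group, at a two-sided 5% level. The calculation is for CVD alone, with no death component.

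**2. Literal reading: any death is an event.** Inputs from the plan are CVD at 1% per year in the unexposed and a ratio of 1.3. Assumed, because the article gives neither, are the non-CVD death rate d in the unexposed (0.25% to 2% per year) and its ratio h for serious mental illness (SMI) (1 to 3). With constant hazards:

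HR = (0.01 × 1.3 + d × h) / (0.01 + d)

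| d per year | h = 1 | h = 1.3 | h = 2 | h = 3 |
|---|---|---|---|---|
| 0.25% | 1.24 | 1.30 | 1.44 | 1.64 |
| 0.5% | 1.20 | 1.30 | 1.53 | 1.87 |
| 1% | 1.15 | 1.30 | 1.65 | 2.15 |
| 2% | 1.10 | 1.30 | 1.77 | 2.43 |

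Example, lower right: (0.013 + 0.02 × 3)/(0.01 + 0.02) = 0.073/0.03 = 2.43. The ratio is diluted when h is below 1.3, unchanged at 1.3 and inflated above it.

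**3. Censoring reading: Cox model.** Non-CVD deaths leave the risk set and are not counted. The cause-specific hazard ratio is 0.013/0.010 = 1.30 whatever d and h are.

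**4. Censoring reading: Kaplan-Meier.** With CVD hazard c and non-CVD death hazard d:

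1 − KM = 1 − exp(−ct)

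Cumulative incidence = c/(c + d) × [1 − exp(−(c + d)t)]

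Unexposed: c = 0.010, assumed d = 0.01. Exposed: c = 0.013, assumed d = 0.02.

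| Time | 1 − KM, exposed v unexposed | Gap, points | Cumulative incidence, exposed v unexposed | Gap, points |
|---|---|---|---|---|
| 3.2 years (median) | 4.07% v 3.15% | 0.93 | 3.95% v 3.10% | 0.85 |
| 4.6 years (mean) | 5.80% v 4.50% | 1.31 | 5.55% v 4.40% | 1.15 |
| 20 years | 22.9% v 18.1% | 4.8 | 19.0% v 16.5% | 2.5 |

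Gaps are taken before rounding. The median and mean come from Sample size calculation, where they describe exposed patients with a weight code in the year before the index date. Follow-up can run to 22 years (Duration of follow-up).

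**The case against.** The best defence is that the intended rule can be recovered from the rest of the article. Objective 3 is CVD incidence and CVD mortality, Table 1 counts only CVD deaths, Duration of follow-up separates death from the outcome, and listing all-cause mortality as its own endpoint would make little sense if every death were already a CVD event. A death date is also a proper outcome date for fatal CVD and for all-cause mortality, so the sentence may be several endpoint rules condensed into one. This stands as a reading of intent. It does not remove the contradiction: the article states two incompatible rules, and neither sentence says which deaths count for which endpoint.

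A reader might infer that the planned SMI–CVD estimate absorbs non-CVD mortality and that Kaplan-Meier adds to the error. The article does not support that. Counting deaths as events and ignoring them as competing events belong to opposite readings and cannot both act on one CVD analysis. Kaplan-Meier does not put non-CVD deaths into the estimate.

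A reader might also infer that the hazard ratio must be inflated. The Introduction reports 15–20 lost years of life and attributes two-thirds of premature mortality to CVD. That makes a non-CVD ratio above 1.3 plausible, but the article gives no such ratio, and step 2 shows dilution below 1.3.

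It is also fair to say that the Kaplan-Meier error is small at the follow-up most patients will have, that few patients would inform a 20-year estimate, and that the choice of competing-risk display may sit in an analysis plan not shown. This keeps the Kaplan-Meier point secondary. It still merits a change, because Kaplan-Meier is the method the article names for total and fatal CVD.

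**Conclusion.** The contradiction is real and should be settled before analysis. Applied literally, the outcome-date rule would give the wrong estimand for objective 3: a hazard ratio of 1.10 to 2.43 where the CVD ratio is 1.30, under constant hazards and the assumed range of non-CVD death. The direction depends on a ratio the article does not supply. The article does not show that the analysis will be run this way, and most of its text points to censoring. On that reading the Cox result is a valid cause-specific hazard ratio.

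The Kaplan-Meier point is separate and arises only if death is censored. The between-group gap in absolute CVD risk is overstated by about 0.08 points at 3.2 years and 2.2 points at 20 years (4.77 − 2.55), under the assumed death rates. The sample size is unaffected on either count.

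**What to change.** Replace the outcome-date sentence with one line per endpoint:

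- Total CVD: first CVD diagnosis or ONS-certified CVD death, whichever is earlier.
- Fatal CVD: ONS-certified CVD death.
- All-cause mortality: death from any cause.

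State that, for the CVD endpoints, any other death is a censoring time in the Cox model, and label the resulting hazard ratio cause-specific. Add a non-CVD group to the cause-of-death categories in Descriptive summaries.

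In Primary analyses, replace the Kaplan-Meier curves for total and fatal CVD with Aalen-Johansen cumulative incidence, with non-CVD death as the competing event. Keep Kaplan-Meier for all-cause mortality.

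The cost is a few lines of text and one extra Stata routine. No new data are needed because the ONS mortality data are already to be linked, and the sample size does not change.

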#### Descriptive summaries

Frequency matching will reduce potential confounding and balance the baseline characteristics of the *exposed* and *unexposed* on age, sex, practice and calendar year. Adequacy of matching will be confirmed by comparing means using independent t-tests. Descriptive statistics will describe the baseline characteristics of patients in the cohort. Categorical data will be presented as frequency and percentages, and continuous variables will be summarised using descriptive statistics mean, standard deviation (SD) or median and interquartile range (IQR). Comparisons between the groups will be made using χ^2^ tests and t-tests (or Wilcoxon rank-sum tests) as appropriate. Length of exposure and the most commonly prescribed class of psychotropic for each patient will be summarised. The causes of death will be categorised as CVD and all-cause mortality.

#### Primary analyses

For objectives 1 and 2, the outcome will be visually inspected by plotting trajectories of weight and cardio-metabolic risk factor change using all repeated measurements for patients with SMI versus patients without SMI. For these analyses, we will use a mixed-effects linear regression model including terms for SMI, time and their interaction to estimate regression coefficients with 95% CIs by SMI status. Models incorporating psychotropic medications will analogously include medication-time multiplicative interaction terms. We will include a random effect for individual and practice identifier to account for intra-class correlation resulting from common practice membership. Diagnostic tests will be conducted to confirm linear regression assumptions are met including linearity of residuals, residual normality using quantile–quantile (Q–Q) plots, and residual heteroscedasticity using residual versus fitted value plots. We will assess for exploratory subgroup effects by adding interactions (eg, by age, sex, ethnicity and SES) and, if significant, we will assess the strength of the associations in separate subgroups for clarity. For objective 2, we will model the association between weight and cardio-metabolic change using restricted cubic splines to allow for non-linear associations. For objective 3, we will use Kaplan-Meier survival estimates for the exposed and unexposed groups to estimate the distribution of time from index date to total and fatal CVD and mortality (all-cause). The statistical equivalence of the two curves will be examined using the log-rank test. This analysis will use a survival from index date between the exposed and unexposed groups using an adjusted Cox proportional hazards regression model with follow-up time as the timescale. Restricted cubic splines will be computed with five knots to visually explore non-linear associations between the exposure and the outcomes. For objective 4, we will use a Poisson regression examining person-time to estimate the rate at which patients who received weight management services over the study period in patients with SMI compared with patients who do not have SMI, adjusting for confounders and BMI.

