The factors underlying excess weight gain in people with SMI are multifactorial. Psychotropic drugs (ie, antipsychotics, antidepressants, mood stabilisers) are the mainstay treatment for the symptoms of psychosis and affect weight.^9^ Evidence from clinical trials has linked these drugs to rapid weight gain, but the long-term effects after a diagnosis are unclear.^9^ In one 11-year follow-up study of people with schizophrenia, increased CVD mortality was reported in people treated with quetiapine (adjusted HR: 1.41, 95% CI 1.09 to 1.82) and reduced CVD mortality in people treated with clozapine (adjusted HR: 0.74, 95% CI 0.60 to 0.91).^10^ However, these estimates may result from unmeasured confounding by socioeconomic and other demographic factors.^11^ Accordingly, a better understanding of the long-term impact of medication on weight change, cardio-metabolic risk factors, and incidence of and mortality from CVD is warranted.

Other factors that cause weight gain include unhelpful dietary patterns and physical inactivity. These behaviours are more common in people with SMI compared with the general population and may reflect the social disadvantage to which SMI contributes.^12^ In addition, the prevalence of smoking is estimated to be twice that in people with SMI compared with general population,^13^ and evidence shows people with schizophrenia smoke more cigarettes per day and more intensely than the general population of smokers.^14^ Other studies using polygenic risk scores for liability to schizophrenia have found no association between those scores and physical health outcomes except for conditions mediated through obesity and smoking.^15^ This suggests that the excess risk to people with SMI are modifiable.

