#### Duration of follow-up

Patients will be followed up in the database from their index date until the earliest of the following: date of death; date of outcome of interest; date of leaving the participating practice; date of the latest download of data; or the end of the study follow-up period (ie, up to 22 years).

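### As stated, the weight and risk-factor models fit one SMI×time slope with no random slope, so they cannot describe early gain, and their slope intervals are too narrow if patients' slopes differ

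*Protocol article*

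**What the plan says.** The Primary analyses section of the protocol article gives both parts of the model for objectives 1 and 2. The fixed part: "we will use a mixed-effects linear regression model including terms for SMI, time and their interaction". The random part: "We will include a random effect for individual and practice identifier to account for intra-class correlation resulting from common practice membership". Models with psychotropic drugs add medication-by-time products in the same way.

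The Statistical analysis section adds: "For objectives 1 and 2, we will use all repeated measures and run separate models for each analyses". Under Duration of follow-up, observation can last 22 years. The Sample size calculation section gives a median of 3.2 and a mean of 4.6 years for exposed patients with a weight recorded in the year before index.

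On the expected course of weight, the Introduction says: "Evidence from clinical trials has linked these drugs to rapid weight gain, but the long-term effects after a diagnosis are unclear".

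Restricted cubic splines are planned for weight against cardio-metabolic change, and for exposure against outcome in the text on objective 3. Neither use concerns time in the repeated-measures models. Trajectories will be plotted by SMI status, and residuals will be checked for linearity, normality and heteroscedasticity. The article does not say what happens if a check fails.

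**The concern.** Two separate problems follow if the model is fitted as stated.

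- **Shape.** Time zero is the first SMI code, when treatment-related gain would be expected to start. A single slope averages the early period with years of later follow-up. It cannot separate rapid gain followed by a plateau from slow steady gain, yet how weight changes over the longer term is the gap the study sets out to fill.
- **Precision.** A random intercept lets patients differ in level but not in rate of change. Real differences in slope are then treated as independent residual noise. The few patients with long follow-up and many weights carry most of the information on slope, and the model credits them with too much precision.

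Weight change is the primary aim of objective 1, and the article adopts an estimation approach, so the coefficient and its interval are the main product.

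**Working it through.** The article gives no figure for this model to reproduce. Its only calculation, n=3907, concerns cardiovascular events.

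**Inputs.** From the protocol: follow-up median 3.2 and mean 4.6 years, maximum 22; up to four unexposed per exposed. Exponential follow-up with mean 4.6 has median 4.6 × ln 2 = 3.19, so it fits the stated pair. Assumed, because the protocol gives none of them: person SD 14–16 kg, residual SD σ = 3 kg, 0.5–2 weights per year, and between-patient slope SD τ of 0–1.5 kg/year.

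**1. Shape.** Suppose SMI adds 5 kg over year 1 and nothing after. Two calculations with about one weight per year gave a main effect of 2.3 kg with slope 0.30 kg/year, and 2.6 kg with slope 0.27 kg/year. Main effect plus slope × years gives the fitted excess:

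| Year | Fitted excess (kg) | True excess (kg) |
|---|---|---|
| 0 | 2.3 to 2.6 | 0 |
| 1 | 2.3 + 0.30 = 2.6; 2.6 + 0.27 = 2.9 | 5 |
| 10 | 2.3 + 3.0 = 5.3; 2.6 + 2.7 = 5.3 | 5 |
| 22 | 2.3 + 6.6 = 8.9; 2.6 + 5.9 = 8.5 | 5 |

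A smoother plateau, 5 × (1 − exp(−t/c)) with c = 0.5, 1 or 2 years, gives slopes of 0.27, 0.31 and 0.35 kg/year. The slope alone then implies about 0.3 kg of change at year 1, against a true 4.3, 3.2 and 2.0 kg.

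**2. Precision.** When person SD is large relative to residual SD, the slope comes almost wholly from within patients. Let S_i be patient i's sum of squared deviations of measurement times from their own mean, and n_i the number of weights. Then:

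- true variance of a group slope = σ²/ΣS + τ² ΣS²/(ΣS)²
- variance the random-intercept model reports = (σ² + τ² ΣS/Σ(n−1)) / ΣS
- (true SE / model SE)² = (σ² + τ² ΣS²/ΣS) / (σ² + τ² ΣS/Σ(n−1))

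Sample size cancels, so a large cohort does not remove the problem. With τ = 0 the ratio is exactly 1.

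*Everyone followed equally, annual weights.*
- 3.2 years (times 0–3; n = 4, S = 5), τ = 1: √[(9 + 5)/(9 + 5/3)] = 1.15.
- 4.6 years (times 0–4; n = 5, S = 10), τ = 1.5: √[(9 + 22.5)/(9 + 5.625)] = 1.47.
- 22 years (n = 23, S = 1012), τ = 0.5: √[(9 + 253)/(9 + 11.5)] = 3.58.

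*Skewed follow-up (exponential, mean 4.6, capped at 22).* The full model-based and sandwich calculation gives these ratios. Coverage of a nominal 95% interval is 2Φ(1.96/ratio) − 1.

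| Weights per year | τ = 0.25 | τ = 0.5 | τ = 1.0 | τ = 1.5 |
|---|---|---|---|---|
| 0.5 | 1.5 | 2.3 | 3.3 | 3.8 |
| 1 | 1.8 | 3.0 | 4.5 | 5.2 |
| 2 | 2.6 | 4.5 | 6.9 | 8.2 |

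At one weight per year, coverage is 72%, 49%, 34% and 29%. Separate calculations at one weight per year, or slightly more, gave 2.0, 3.1–3.2 and 4.8–5.3 for the first three slope SDs.

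**The case against.** **The form is inferred.** The article does not use the words straight line or random intercept. It is a condensed text, and time coding and covariance structure are often left to an analysis plan. This stands as a reason to say natural reading rather than proven fact. But the article does state both the fixed and the random part, and where it wants splines it says so, for other relations.

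**The outcome is change.** Table 1 defines the outcomes as change, so an SMI main effect need not be read as a baseline difference. This stands: how the offset would be read depends on whether weights or changes from baseline are modelled. It does not rescue the fit. Even with main effect and slope added together, the example gives 2.6–2.9 kg at year 1 and 8.5–8.9 kg at year 22, when the truth is 5 kg at both.

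**Plots and residual checks.** A reader might infer that early gain would be hidden. The documents do not support that, since trajectories are plotted for both groups and a sharp rise could be seen. But the reported estimate would still be one slope, any remodelling would be chosen after seeing the data, and plots do not correct standard errors.

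**The cohort is very large.** In a simulation of 400 patients at 1:4 (80 exposed), the true SDs of the slope difference were 0.223 and 0.363 kg/year for slope SDs of 0.5 and 1.0. Scaled to the 135 870 exposed patients cited, 1.96 × 0.223 × √(80/135 870) = 0.011 and 1.96 × 0.363 × √(80/135 870) = 0.017 kg/year. So a correct interval for the main SMI contrast could still be narrow. That stands, although the count is before exclusions and smaller medication contrasts would be affected more. It makes the shape problem the weightier one for the main contrast.

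**Conclusion.** The point holds on the natural reading of the Primary analyses section. One slope over up to 22 years cannot describe the course that the Introduction expects. With a 5 kg excess gained in year 1 and then held, the reported slope would be about 0.3 kg/year, with about 2.3–2.6 kg in the SMI main effect. Both figures rest on the assumed gain, follow-up distribution and weighing frequency.

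Intervals for SMI×time and medication×time are too narrow whenever patients' slopes differ. A reader might infer that they are several times too narrow as a matter of fact. The protocol gives no slope SD, residual SD or weighing frequency, so that is not established. The range is about 1.5–8 for slope SDs of 0.25–1.5 kg/year with skewed follow-up, 1.0–1.5 if everyone had only 3.2–4.6 years of annual weights, and 1.0 with no slope variation. The gap between the stated median and mean points to skewed follow-up.

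**What to change.** Before analysis, for objectives 1 and 2:

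1. Model time with restricted cubic splines or a piecewise form that gives detail in the early period, with SMI interactions, and treat the medication-by-time terms in the same way. Knot placement is a choice; it should be fixed in advance.
2. Report the SMI-minus-unexposed contrast with its interval at fixed times, for example 1, 2, 5 and 10 years, as the primary result.
3. Add a patient-level random slope for time, correlated with the intercept. If it does not converge, use cluster-robust standard errors.
4. State whether weights or changes from baseline are modelled, so that the SMI main effect has a defined meaning.

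The cost is longer computing time on a large dataset and a less simple summary than one slope. No new data are needed.
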